### Patients' characteristics

At baseline the following characteristics of patients are registered: socio-demographics (sex, age and educational level), diagnosis, SQ-48 (ROM) score, previous treatment, length of waiting time and the motivation to start treatment (own initiative or by pressure of the social environment). At T2, patients will receive a self-report questionnaire with a single question about the extent to

which their personal treatment goals have been achieved. This question has three response categories (yes, partially, no).

EPR = Electronical Patient Records

### Primary outcome measure

The primary outcome measure is the degree of decisional conflict a central determinant of decision making, which is defined as 'personal uncertainty about which option to choose' [55, 56], will be measured with the translated Decisional Conflict Scale (DCS) [18, 55]. The DCS is a self-report questionnaire comprising sixteen questions about personal perceptions of: uncertainty in choosing options, modifiable factors contributing to uncertainty, effective decision making such as feeling the choice is informed, values-based, likely to be implemented and expressing satisfaction with the choice [55]. Each item is measured on a 5-point Likert scale (0 = strongly agree to 4 = strongly disagree). Besides the total score, the DCS has the following five subscales: uncertainty, informed, values clarity, support and effective decision. To calculate the total and subscale scores the item scores will be averaged and multiplied by 25. The

[figure not shown]

scores thus range from 0 (no decisional conflict) to 100 (extremely high decisional conflict).

The psychometric properties of the English version of the DCS are adequate. Test-retest reliability (0.81) and Cronbach alpha (0.78) are high. The scale correlates to related constructs (knowledge, regret, discontinuance) and discriminates between groups who make and delay decisions (construct validity). DCS is responsive to change between different decision supporting interventions. The predictive validity of the DCS is also demonstrated [44, 55, 56].

To compare the degree of decisional conflict (or agreement) between patients and clinicians about the decisions made, at T1 both patients and clinicians fill out a Visual Analogue Scale (VAS).

### Secondary outcome measures

The secondary outcome measures are patient participation, process of shared decision making, working alliance, patients' adherence to treatment and clinical outcome.

The research team developed the Patient Participation Questionnaire (PPQ), because no accessible, brief instrument was found that measures patient participation in treatment with good psychometric properties and which is also suitable to fill out during or just after the intake process of mental health treatment.

The PPQ measures the role of the patient in treatment and shared decision making, consists of 14 items and is filled out by patients. Each item is measured on a five

point Likert scale (1 = totally not applicable to 5 = totally applicable). Item scores will be summed. A higher score indicates a more active role of the patient in the interplay with the clinician and in mental health treatment. Three sample items of the PPQ include:

'Along with my clinician I have described my treatment targets'.

'I participate actively in my treatment'.

'I participate in decisions about my treatment'.

After development, the PPQ was tested on nine clinicians and three peers working at GGz Breburg. They were asked to fill out the questionnaire and were interviewed afterwards for feedback. The aim of testing was to see if the items are relevant and comprehensible. This feedback resulted in textual improvements and adjustments in the order of the questions. The psychometric qualities of the questionnaire will be investigated in the population of this study: the factor structure, the reliability (test-retest and internal consistency) and construct (convergent) validity of the instrument [57, 58]. Convergent validity will be tested using

- 1) Decisional Conflict Scale (DCS) [55];
- 2) Visual Analogue Scale (VAS) consisting of one item filled out by patients, about the active role of the patient in treatment measured on a scale from 1 to

- 10 (1 = not at all to 10 = completely). A higher score means a more active role in mental health treatment;
- 3) two items about treatment targets of the Patient Reported Experience Measure (PREM) for chronic care [59, 60]. The items describe the joint formulation of treatment goals and how to achieve these goals. This self-report questionnaire is filled out by patients on a 5-point Likert scale (1 = completely disagree to 5 = completely agree);
  - 4) Shared Decision Making-Questionnaire-9 (SDM-Q-9) [61–63] and
  - 5) Patient-Doctor Relationship Questionnaire (PDRQ-9) [64].

The SDM-process will be measured with the Shared Decision Making-Questionnaire-9 (SDM-Q-9) [61, 62], which has Dutch versions for patients and clinicians [18, 63]. Both versions ask the patient and clinician first to enter the health problem the consultation was about and which decision was made. The questionnaire continues with nine items about the steps in the SDM process, scoring at a 6-point Likert scale that ranges from 0 (completely disagree) to 5 (completely agree). A total score can be calculated by summing the scores of all items. A high score indicates more SDM. The SDM-Q-9 shows a high reliability [61, 62]. The available results about the factorial validity are also positive [61, 62]. The psychometric testing of the Dutch version of the SDM-Q-9 [63] demonstrated good acceptance, internal consistency, and acceptable to good convergent validity of the versions for patients and physicians. Patients will be asked to complete the SDM-Q-9 at T1 and T2. At T1 clinicians will complete the same questions regarding the consultations with their patients.

The PDRQ-9 will measure the working alliance. The PDRQ-9 consists of 9 items and measures the therapeutic aspects of the clinician-patient relationship from a patient point of view. The items focus on the empathic style and availability of the clinician and are answered on a 5-point Likert scale (1 = not at all appropriate to 5 = totally appropriate). Two sample items are: 'My clinician understands me' and 'My clinician and I agree on the nature of my medical symptoms'. A mean score of all nine items is calculated. A higher score means more satisfaction about the relationship. The psychometric quality of the Dutch PDRQ-9 shows good internal consistency, adequate test-retest reliability and the ability to discriminate between patient groups [64].

Next the patients' adherence to treatment will be investigated. Adherence can be defined as the extent to which the patient's behaviour concur with the advice of the clinician [9]. In this study adherence is operationalised as the number of missed appointments (no-shows) and patients who do not want to proceed with treatment

(early treatment drop out). These data will be extracted from the electronic patient records.

Finally, effects on treatment results will be studied with the Symptom Questionnaire-48 (SQ-48). This is a self-report questionnaire for the measurement of psychological distress, vitality and work functioning and consists of 48 items. Each item is rated on a 5-points Likert-scale (0 = Never to 4 = Very often). Five subscales cover aspects of psychopathology: Depression, Anxiety, Somatization/Somatic complaints, Social Phobia and Agoraphobia. In addition, four subscales were constructed to assess specific aspects of behaviour and/or functioning: Aggression, Cognitive problems/complaints, Work and Vitality. The total score is calculated by summing 37 items (excluding work and vitality subscale-items) and ranges from 0 to 148, with higher scores indicating more psychological distress. The subscales work and vitality have a different scoring (Work with answering options "not applicable"; Vitality which scoring is reversed for the positively formulated items).

Research demonstrated the quality of the psychometric properties of the SQ-48. The internal consistency (reliability) as well as the convergent and divergent validity among both clinical and nonclinical samples are good [65]. Research also showed that the SQ-48 has excellent test-retest reliability and good responsiveness to therapeutic change [66].

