## Aim and hypotheses

Aim of this trial is to test the efficacy of a digital exploration of patients’ treatment preferences at intake facilitated by Routine Outcome Monitoring (ROM), peer support and training of clinicians in terms of the primary outcome the degree of decisional conflict, as an important result of patient participation and shared decision making [26, 44]. This manuscript will report on the development of this new digital intake approach and the design of the study that will be conducted to evaluate this approach.

The first hypothesis is that, compared to the intake as usual, the new intake method will lead to less decisional conflict about choices in treatment. The second hypothesis is that the implementation of the new intake method

enhances patient participation, stimulates the process of shared decision making, improves the working alliance between patients and clinicians, and finally has positive effects on the adherence to treatment and clinical outcomes.

Methods/Design

Trial design

This study is designed as a two-arm matched-pair cluster-randomised controlled trial with two conditions: 1. A digital intake process with eHealth interventions integrated with two consecutive Routine Outcome Monitoring (ROM) measurements and consultation of peers supporting patients to participate from the beginning of treatment along with training and coaching of clinicians to adopt the changing roles; 2. The intake as usual with a single ROM measurement and without eHealth interventions, peer support and training of clinicians. The control teams will implement the new intake process after the completion of the data-collection.

Participants and setting

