out the eHealth modules, patients get the opportunity to have contact with peers (by phone or mail) who can support and prepare them for the intake consult. Peers have life experience with mental illness and treatment. They are already working at GGz Breburg and are experts in supporting patients. They have completed specific education about how to support patients using their experience in mental health care and get also instruction in the way to assist patients who are following eHealth. To prepare for the first consultation, the completed modules are visible for both the patient and the clinician. During this first intake consultation patients and clinicians discuss results of the first pre-intake module by exploring the burden and impact of the mental health problems on daily life. During the second face to face consultation patient and clinician complete, using the results of the second module, the exploration about problems, coping and goals and take shared decisions about the treatment policy and goals. After the second intake consultation the treatment starts. In both conditions the number of face to face contacts in the intake procedure are the same. To make sure that patients and clinicians have sufficient time to discuss the results of the eHealth module, in the new intake approach the first intake consult will take 30 min longer. Because ROM is a promising tool which visualises symptoms severity and functioning, stimulates effective communication between

[figure not shown]

patients and clinicians and empowers patients [49, 53] in the new digital intake approach an additional ROM moment is planned. While the intake as usual includes a single ROM measurement linked to the face to face intake consultation, the new intake approach includes two measurements: one measurement incorporated in the first eHealth module and one, as usual, linked to the face to face intake consultation. In both conditions the multidisciplinary team consultation keeps a role in checking the quality and appropriateness of the proposed treatment and process steps, according to multidisciplinary guidelines.

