### Study flow

Patients who are referred to one of the participating departments, are invited for an intake consult. Patients

who are planned for an intake consultation with a clinician of the intervention group, are assigned to the intervention team and will get the new eHealth intake automatically. Patients who have this first appointment with a clinician of the control group, are assigned to the control group and will follow the intake as usual. In addition, both groups of patients, who follow the new intake process and the intake as usual, will be invited to participate in the evaluation research consecutively. Research assistants inform all patients (who meet the inclusion criteria) about the research, ask them to participate in the study and obtain written informed consent.

Three measurement points will be scheduled (see Table 2): baseline assessment (T0) and two measurements (T1, T2) after the intake (T1 = two weeks after intake, T2 = two months after intake). Because only T1 and T2 contains additional questionnaires for this research, written informed consent will be asked during the first face to face appointment, just before T1. Patients who give informed consent for the research, are completing self-report questionnaires organised by independent research assistants. In addition to T1, clinicians answer questions about shared decision making regarding their patients. Patients and clinicians who participate in the study, receive a request by email to complete the questionnaires. If necessary, one week later they get a reminder by email. After nine and fourteen days the research assistant calls patients who have not yet

**Table 2** Measurement points

| Assessment/Questionnaire                                                                                                                    | Baseline (T0) | 2 weeks after intake (T1) | 2 months after intake (T2) |
|---------------------------------------------------------------------------------------------------------------------------------------------|---------------|---------------------------|----------------------------|
| Primary Outcome Parameter                                                                                                            |               |                           |                            |

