| Decisional Conflict                                                                                                                         |               |                           |                            |
| Decisional Conflict Scale patient                                                                                                           |               | X                         | X                          |
| VAS patient (additional)                                                                                                                    |               | X                         | X                          |
| VAS clinician (additional)                                                                                                                  |               | X                         |                            |
| Secondary Outcome Parameters                                                                                                         |               |                           |                            |
| Patient participation in mental health (treatment).
Patient Participation Questionnaire                                                  |               | X                         | X                          |
| Shared Decision Making process
SDM-Q-9 Patient and clinician.                                                                            |               | X                         | X                          |
| Working alliance
PDRQ-9                                                                                                                  |               | X                         | X                          |
| Adherence to treatment
Drop-out, no-show                                                                                                 |               | EPR                       | EPR                        |
| Symptoms-functioning
SQ-48 (=ROM)                                                                                                        | X             | X                         | X                          |
| Patients' characteristics                                                                                                            |               |                           |                            |

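### The two PPQ administrations, about six weeks apart in early treatment, can show stability but cannot support the promised test-retest reliability

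*Protocol*

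**What the plan says.** Under Secondary outcome measures, the Protocol introduces the PPQ as a 14-item patient questionnaire made by the research team. Before the trial it was tried on nine clinicians and three peers, to see whether the items were relevant and understandable. The formal validation is left to the trial: "The psychometric qualities of the questionnaire will be investigated in the population of this study". It is to cover the factor structure and "the reliability (test-retest and internal consistency) and construct (convergent) validity of the instrument".

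Under Study flow, the measurement times are "T1 = two weeks after intake, T2 = two months after intake". The Table 2 row "Patient participation in mental health (treatment). Patient Participation Questionnaire" is marked at T1 and T2 and blank at baseline. The text agrees that there is no other occasion: "Because only T1 and T2 contains additional questionnaires for this research".

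Under Intervention and control, the order of events is given: "After the second intake consultation the treatment starts".

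On what the scale measures, Secondary outcome measures says: "A higher score indicates a more active role of the patient in the interplay with the clinician and in mental health treatment". Under Aim and hypotheses, patient participation is also something the new intake is meant to raise; the second hypothesis is that it "enhances patient participation, stimulates the process of shared decision making, improves the working alliance between patients and clinicians".

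**The concern.** Test-retest reliability is the agreement between repeated measurements of something that has not changed. It needs an interval over which the construct can be taken as stable, or a way to identify patients who were stable. The Protocol promises the quantity and fixes a schedule that provides neither. The PPQ asks about the patient's part in treatment, and its two administrations span the first weeks of that treatment. If some patients become more active and others less so, the T1-T2 coefficient falls for reasons unrelated to the quality of the questionnaire.

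What is at stake is the conclusion about the instrument. The Protocol cites no earlier psychometric evidence for the PPQ. For the other scales it reports retest evidence: 0.81 for the Decisional Conflict Scale, and favourable descriptions for the PDRQ-9 and SQ-48. A PPQ coefficient published under the same name would be compared with those, and a sound questionnaire could be judged less reliable than it is.

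An analysis plan could relabel or qualify the coefficient, but it cannot supply a retest occasion that the schedule does not contain.

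**Working it through.** **Interval.** Inputs are T1 = 2 weeks and T2 = 2 months after intake (Study flow).

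- Calendar months: 2 × 365.25/12 = 60.9 days; 60.9 − 14 = 46.9 days; 46.9/7 = 6.7 weeks.
- Four-week months: 56 − 14 = 42 days = 6.0 weeks.
- Reminders run to 14 days after the request. If one of the two responses slips by 14 days, the calendar-month interval for that patient becomes (46.9 − 14)/7 = 4.7 weeks or (46.9 + 14)/7 = 8.7 weeks.

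The nominal gap is thus about six to seven weeks. The Protocol states no retest interval, stability criterion or reliability figure for the PPQ, so there is no figure of its own to reproduce.

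**Position relative to treatment.** Treatment follows the second intake consultation. If intake means the completed intake, T1 and T2 both fall after that point. If it means the first consultation, the interval may straddle the start of treatment. On either reading it includes early treatment.

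**What the coefficient estimates.** Assume equal reliability at both occasions and measurement errors that are independent between them. Then

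expected T1-T2 correlation = reliability × true-score stability,

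where stability is the correlation between true scores at T1 and T2. Only if stability is 1 does this equal test-retest reliability.

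**Illustration (assumed inputs; the Protocol gives none).** Reliability 0.85:

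| True-score stability | Expected T1-T2 correlation |
|---|---|
| 1.0 | 0.85 × 1.0 = 0.85 |
| 0.9 | 0.85 × 0.9 = 0.765 |
| 0.7 | 0.85 × 0.7 = 0.595 |
| 0.5 | 0.85 × 0.5 = 0.425, about 0.43 |

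**Why the data cannot resolve it.** There is one observed correlation and there are two unknowns. An observed 0.63 fits a mediocre scale with little change (0.70 × 0.90 = 0.63) and a good scale with more change (0.90 × 0.70 = 0.63) equally well. Table 2 has no third occasion and no short repeat to tell these apart.

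**Mean change.** A uniform shift leaves a Pearson or consistency coefficient unchanged; only differences between patients in how much they change lower it. An agreement coefficient is also lowered by a uniform shift. With equal variances it is reliability × stability / (1 + shift²/2), the shift being in observed-SD units. At reliability 0.80 and stability 1.0, a shift of 0.3 gives 0.80/1.045 = 0.77, and a shift of 0.5 gives 0.80/1.125 = 0.71. The Protocol does not say which coefficient is meant.

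**The case against.** The strongest reply is that change between T1 and T2 is not documented. The second hypothesis compares arms; it does not predict movement after T1. The modules and both intake consultations are complete before treatment starts, so any effect of the intake on participation may already be present at T1. One sample PPQ item concerns describing treatment targets with the clinician, which belongs largely to the second consultation. The team also wanted an instrument usable during or just after intake. If participation is settled by T1, stability is close to 1 and nothing is lost. This stands as a limit on wording: the coefficient could understate reliability, and nobody can say from the Protocol that it will. It does not remove the problem, because other sample items concern ongoing participation in treatment and the design cannot show which case applies.

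It is also true that no decision in the Protocol hangs on the coefficient, that the PPQ's use as an outcome carries no reliability threshold, and that internal consistency, factor structure and convergent validity can be estimated at one time point. That keeps the point minor.

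Two stronger readings are tempting. A reader might infer that the arms will be pooled, so that a shared treatment effect inflates the convergent-validity correlations. The Protocol lists the comparator instruments but does not say that the arms will be pooled, gives no effect size for the PPQ, and may properly leave this to the analysis plan. A reader might also infer that the PPQ comparison between arms is compromised. Nothing here supports that: the point concerns the label on a psychometric coefficient.

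**Conclusion.** The concern holds as a mismatch between a promised quantity and the schedule that is to supply it. The Protocol offers test-retest reliability from two administrations 6.0 to 6.7 weeks apart in early treatment, with no means of separating measurement error from real change in the patient's role. The resulting coefficient is a measure of stability.

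Its size cannot be derived from the document. Under the assumed reliability of 0.85, the expected coefficient runs from 0.85 with no differential change to about 0.43 at a stability of 0.5. These figures rest on the stated assumptions and do not forecast the result. The likely direction is downward, so the coefficient can serve as a likely lower bound on test-retest reliability. It is only a likely bound, because errors correlated between occasions, such as a persistent response style, would push the other way.

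The matter is minor. It concerns the validation of one secondary instrument and leaves the primary outcome, the sample size and the treatment comparison as they are.

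**What to change.** In the Protocol, Secondary outcome measures, take test-retest out of the list of PPQ reliability analyses. In its place, state that the T1-T2 coefficient will be reported as stability over about six weeks and read as a likely lower bound on test-retest reliability. State also that the reliability claim for the PPQ rests on internal consistency at a single, named time point.

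The cost is one changed sentence and no new data. The downside is that the trial makes no test-retest claim; internal consistency concerns agreement among items and does not replace evidence on repeatability over time.

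Restricting the T1-T2 analysis to patients whose active-role visual analogue score is unchanged is not a good substitute. The Protocol does not clearly schedule that item at both times. It is also one of the PPQ's own validity criteria, and selecting on a single error-prone item from the same respondents could itself bias the coefficient.

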A cluster randomised design at the level of intake-teams and participation of intake-teams in separate multidisciplinary consultations will serve to limit contamination effects between intervention and control groups [45]. The pairs of intake groups within a department are randomly assigned to either the experimental or control condition (matched pairs). The matched teams within each department perform intakes for a similar population of patients in a similar geographic catchment area and have similar personnel. Randomisation of the intake-teams is conducted by an independent researcher, using a syntax in SPSS, which allocates the matched pairs to the control (code 0) or intervention group (code 1). To reduce bias, data collection for this study will be carried out by research assistants, independent of the principal investigator and treatment, with self-report instruments completed by both patients and clinicians. This results are not visible at patient level during intake and treatment. Only the outcome parameters no-show, drop-out and clinical outcome (ROM) will be collected in the context of treatment. As is common practice in cluster randomised RCTs, propensity analyses will be performed at the analytical stage to correct for possible biases in the randomisation process [45].

During inclusion, while informing patients and asking them for written informed consent, the research assistants are blinded for the study arm. The questionnaires

[figure not shown]

Fig. 1 Participating departments and intake teams

are based on self report and hence do not require assessment by a research assistant. Due to the randomisation at the team level and the nature of the intervention, blinding of the clinicians and patients is impossible.

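### The no-show component of the adherence outcome is a raw count with no denominator, so a difference in drop-out between the arms distorts the no-show comparison

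*Protocol*

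**What the plan says.** The protocol's Secondary outcome measures section gives a concept of adherence and then a way of measuring it. The concept is one of degree: "Adherence can be defined as the extent to which the patient's behaviour concur with the advice of the clinician". For measurement, "adherence is operationalised as the number of missed appointments (no-shows) and patients who do not want to proceed with treatment", the latter glossed as "early treatment drop out). These data will be extracted from the electronic patient records".

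Table 2 (Study flow) lists "Drop-out, no-show" under adherence, from the patient records at T1 and T2, where "T1 = two weeks after intake, T2 = two months after intake". Randomisation and blinding names the same two items separately: "Only the outcome parameters no-show, drop-out and clinical outcome (ROM) will be collected in the context of treatment". The Discussion repeats this. The second hypothesis in Aim and hypotheses is that the new intake "has positive effects on the adherence to treatment and clinical outcomes".

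None of these places mentions the number of appointments scheduled or the time a patient remained in treatment. Statistical analyses names multi-level analysis for the hypotheses and says nothing specific about no-shows.

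**The concern.** A no-show can occur only at an appointment that was scheduled. Once a patient leaves treatment, the count stops growing. One of the two adherence parameters (drop-out) therefore mechanically lowers the other (no-shows).

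If the new intake improves retention, as the protocol hopes, its patients accumulate more appointments and hence more chances to miss one, so the raw count works against the intervention. If it worsens retention, the count flatters it. Either way, the no-show comparison mixes attendance behaviour with length of exposure. A degree of concordance, which is how the protocol describes adherence, needs an opportunity base that a raw count lacks.

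**Working it through.** The protocol states no no-show rate, treatment drop-out rate or number of appointments, so there is no figure to reproduce. What follows is an illustration; every input is assumed.

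**Notation.** S = appointments scheduled up to T2 for a stayer; k = the same for an early quitter; p = chance that a stayer misses an appointment; q = the same for a quitter; d = share of an arm that quits early.

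**Per patient.** Expected no-shows are p × S for a stayer and q × k for a quitter. With S = 6 to 10, k = 2 to 3 and p = q = 0.1 to 0.3:
- stayer: 0.1 × 6 = 0.6 up to 0.3 × 10 = 3.0;
- quitter: 0.1 × 2 = 0.2 up to 0.3 × 3 = 0.9.

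At p = 0.2, S = 8, k = 2, a stayer has 1.6 and a quitter 0.4. A quitter who misses at twice the rate (q = 0.4) still has only 0.8. Per scheduled appointment the values are 0.20 for the stayer and 0.40 for that quitter, which is the right order.

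**Per arm.** Mean no-shows = pS(1 − d) + qkd = pS − d(pS − qk).

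With q = p, S = 8, k = 2 this is p(8 − 6d), and p cancels in the ratio of arms:

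| Drop-out, worse v better arm | Better arm | Worse arm | Ratio, better/worse |
|---|---|---|---|
| 30% v 10% | 7.4p | 6.2p | 1.19 |
| 30% v 20% | 6.8p | 6.2p | 1.10 |
| 20% v 10% | 7.4p | 6.8p | 1.09 |

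So the arm that retains more patients shows about 9% to 19% more no-shows with identical attendance behaviour.

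**Sensitivity to k.** With S = 8, k = 3, p = 0.15 and 30% v 10% drop-out:
- worse arm: 0.15 × (0.3 × 3 + 0.7 × 8) = 0.975;
- better arm: 0.15 × (0.1 × 3 + 0.9 × 8) = 1.125.

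The ratio 0.975 / 1.125 = 0.867, that is 13% fewer no-shows in the arm that loses more patients.

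**When the direction changes.** From the arm formula, the count falls with d only while pS > qk, that is while q/p < S/k. At S = 8, k = 3, p = 0.15 the break-even is q = 0.15 × 8/3 = 0.40. At that miss rate in quitters the artefact is gone, and above it the artefact reverses. Over S = 6 to 10 and k = 2 to 3, the break-even ratio q/p runs from 6/3 = 2 to 10/2 = 5.

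**How visible it would be.** Take the k = 3 scenario with the planned 88 per arm, ignoring clustering, which would widen both standard errors.
- No-shows: variance = p(1 − p) × mean appointments + p²(S − k)²d(1 − d). Better arm: 0.1275 × 7.5 + 0.0225 × 25 × 0.09 = 1.01. Worse arm: 0.1275 × 6.5 + 0.0225 × 25 × 0.21 = 0.95. SE = √((1.01 + 0.95)/88) = 0.149; z = 0.15/0.149 ≈ 1.0.
- Drop-out: SE = √((0.3 × 0.7 + 0.1 × 0.9)/88) = 0.058; z = 0.20/0.058 ≈ 3.4.

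**The case against.** **Drop-out is measured too.** A reader might infer that an early quitter simply looks more adherent and that the sign of the adherence effect could be reversed. The documents do not support that. Drop-out is the second parameter, listed in its own right in Table 2, in Randomisation and blinding and in the Discussion, and nothing merges the two into one score. A quitter is recorded as non-adherent there. In the worked scenario the drop-out difference is plain (z about 3.4), while the no-show artefact would hardly stand out from noise (z about 1.0). This objection stands and confines the point to the no-show component. It does not repair that component, which would still be reported as evidence on adherence.

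**The model belongs in the analysis plan.** This is fair as regards distribution, link and offset, and a plan that is not shown may settle them. But the definition of the outcome and the data to be taken from the records are stated in the protocol, and neither includes scheduled appointments. An offset cannot be fitted if that field is not extracted.

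**The arms are otherwise comparable.** The follow-up window is fixed, the number of face-to-face intake contacts is the same in both conditions, and teams are paired within department. Varying appointment numbers alone therefore need not bias the comparison; the concern is differential drop-out. The equality of contacts is stated only for the intake procedure, however, and treatment starts after the second intake consultation.

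**The direction rests on an assumption.** This also stands: quitters may miss more often than stayers, and beyond the break-even the distortion reverses. That makes the raw count harder to interpret, not safer.

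**Conclusion.** The point holds for the no-show component only. As defined, it is a count without a denominator, and a difference in drop-out between arms would distort it. The arm with more drop-out is favoured when quitters miss at a similar rate per appointment. The size is unknown; about 9% to 19% is an illustration under S = 8, k = 2, equal miss rates and drop-out differences of 10 to 20 percentage points. If drop-out is similar in the two arms, the distortion is small whatever the other inputs.

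This is one component of one secondary outcome. It does not reverse adherence as a whole, and it touches neither the primary outcome nor the sample size. It is worth correcting because the correction is cheap and the second hypothesis makes a claim about adherence.

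**What to change.** Redefine the no-show outcome as missed appointments out of appointments scheduled up to T2. Within the planned multi-level analysis, fit it as a binomial outcome, or as a count with the log of scheduled appointments as offset. Add the number of scheduled appointments to the extraction from the electronic patient records. State that the no-show result is to be interpreted alongside drop-out, which stays as the separate parameter it already is, because a rate per scheduled appointment describes attendance only while appointments are being made.

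The cost is one additional extracted field. This assumes that the records hold a usable count of scheduled appointments, which the protocol does not say and which should be checked first.
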